#### Additional measures

Additional measures include demographic information comprising age, sex, gender, cultural and linguistic diversity attributes, academic performance, and truancy rates. To measure socioeconomic status, students will complete the Family Affluence Scale III [62] and provide their home postcode, which will be used in addition to each school’s Index of Community Socio-Educational Advantage score. Alcohol use will be assessed using items from our previous trials [39]. Emotional regulation will be measured using the Emotion Regulation Questionnaire for Children and Adolescents [63].

#### Process evaluation

After the final lesson of the *OurFutures Vaping Program*, students and teachers in the intervention group will be asked to complete an online questionnaire to evaluate the program, and teachers will complete a logbook to assess fidelity and implementation barriers and facilitators. Using measures developed and employed in our previous school-based trials [64], the student evaluation will assess outcomes including acceptability, feasibility, engagement, and positive/negative aspects of the *OurFutures Vaping Program*. Teacher outcomes will include adherence to the intervention, student engagement and understanding, program acceptability, ease of use, educational quality, likelihood of use in the future, and any barriers or enablers to implementation. Website analytics will provide objective data on the dose and timing of intervention delivery.

### Analysis

#### Intervention effects

Data analysis will be conducted on an intention-to-treat basis, whereby all randomised students will be analysed in the groups that they were originally assigned. Generalized mixed effects regression will investigate whether receiving the intervention reduces the likelihood of primary and secondary outcomes (e.g., logistic regression for dichotomous outcomes, poisson regression for count outcomes, linear regression for continuous outcomes). Analyses will be conducted in R, using the *lme4* package [65]. To account for within-person and within-school dependency in the data, models will include participant and school as nested random intercepts; and participant and time as random slopes. We will also test different specifications of time (linear, quadradic & categorical) to determine the best fitting model for the data. Model fit will be compared using likelihood ratio tests, AIC and BIC statistics. The effect of greatest interest will be the time × group interaction for the primary outcome, which reflects the relative average 12-month change in the log odds of the outcome for the intervention group compared to control, adjusting for baseline differences. Due to loss to follow-up, we reasonably expect some outcome data to be missing. Mixed-effects models use maximum likelihood estimation (MLE), producing unbiased estimates when data is assumed to be not missing completely at random. Missing data will be explored by examining baseline differences on the outcome and other potential confounding variables between those retained and those lost to follow-up. Sensitivity analysis will examine the impact of potential covariates related to missingness by including those predictors in the imputation model during multiple imputation.

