## Method

### Study design

A two-arm cluster RCT will be conducted among Year 7 and 8 students in 42 secondary schools across New South Wales (NSW), Western Australia (WA) and Queensland (QLD), Australia, from 2023 to 2026. Cluster randomisation at the school level will be used to avoid potential contamination of the control group by the intervention group (e.g., due to student communication). This design allows for optimal and rigorous evaluation of the research questions and hypotheses. Schools will be randomly allocated (1:1) to either the *OurFutures Vaping Program* intervention group or an active control (health education as usual). An economic evaluation will be conducted alongside the cluster RCT to determine the cost-effectiveness of the OurFutures Vaping Program. The study is sponsored by the University of Sydney and has been approved by the Human Research Ethics Committees of the University of Sydney (2022/818), University of Queensland (2023/HE000082) and Curtin University (HRE2023-0059). The trial will follow Consolidated Standards of Reporting Trials (CONSORT) guidelines for cluster RCTs and has been prospectively registered with the Australian and New Zealand Clinical Trials Registry (ACTRN12623000022662), with any modifications logged immediately. This protocol follows Standard Protocol Items: Recommendations for Interventional Trials (SPIRIT) guidelines (see Additional File 1 SPIRIT checklist).

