### Sample size calculations

The sample size calculations are based on a method to detect intervention by time interactions in longitudinal cluster RCTs [33]. To detect differences by state, and between groups across the six measurement occasions, six schools and 420 students will be randomly allocated to each of the control and intervention groups in each state (12 schools; 840 students per state). This will achieve 95% power to detect an Odds Ratio (OR) of 0.7 in the primary outcome, which is in line with effect sizes from similar school-based prevention trials targeting tobacco smoking [34, 35]. To account for school dropout (approx. 15%) and student attrition (approx. 25% over 36 months), we aim to recruit a minimum of 14 schools and 1,120 students per state at baseline to test intervention effects (N = 42 schools; 3,360 students). Based on rates in our previous school-based universal substance use prevention trials and successful recruitment strategies [36], we anticipate most, if not all, students will participate.

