#### Randomisation

The *blockrand* package in R [37] will be used to generate an unpredictable, concealed random allocation sequence. After schools’ consent and enrolment in the study, a biostatistician with no role in school recruitment will use the package to block randomise schools to study groups, with stratification by state and school gender mix (coeducational, predominately male [> 60%], or predominately female [> 60%]). Automatic randomisation removes any researcher involvement, and the allocation will be concealed from the investigators and all research personnel (blinded), except those with direct school involvement where blinding is not possible (e.g., Research Assistants who will need to discuss intervention delivery with teachers). Twenty-one schools will be randomly allocated to the *OurFutures Vaping Program* intervention group and 21 schools to an active control group. Figure 1 provides an overview of the anticipated recruitment and randomisation process, and Table 1 presents the SPIRIT flow diagram schedule of enrolment, interventions, and assessments.

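### The random-effects sentence is malformed and gives school no random effect for time, so the primary time × group test is anti-conservative as written whenever schools differ in change

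*Protocol article*

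**What the plan says.** Under Study design, the Protocol article makes the school the unit of randomisation: "Cluster randomisation at the school level will be used to avoid potential contamination of the control group". Under Intervention effects it names the primary contrast: "The effect of greatest interest will be the time × group interaction for the primary outcome". It describes this as the relative average 12-month change in log odds between the groups. For dependency within persons and within schools, the same section says "models will include participant and school as nested random intercepts; and participant and time as random slopes", with models fitted in lme4. Time may be coded as linear, quadratic or categorical according to fit. No corresponding step is described for choosing or extending the random effects.

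**The concern.** The sentence fails in two ways. First, participant identifies groups of repeated observations. It can carry an intercept or a time slope, but it cannot itself be a slope, so the sentence cannot be coded as printed. Second, school appears only among the intercepts.

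The second matters more. A school intercept shifts all of a school's measurements equally and so contributes nothing to change from baseline. A participant time slope does not replace the missing term: slopes are taken as independent between students, so they average out over the students in a school, whereas a movement shared by the whole school does not. The interaction would be tested as if students in the same school changed independently. At stake are the primary p-value and confidence interval: the standard error would be too small and the interval too narrow.

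**Working it through.** **The plan's own figure.** Under Sample size calculations, "The sample size calculations are based on a method to detect intervention by time interactions in longitudinal cluster RCTs", with "six schools and 420 students will be randomly allocated to each of the control and intervention groups in each state" and "This will achieve 95% power to detect an Odds Ratio (OR) of 0.7 in the primary outcome". The article does not give alpha, control rate, ICC or within-person correlation, so the 95% can be neither reproduced nor refuted. One set of assumptions comes close for a single state:

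- Assumed: two-sided 5% test, six equally spaced visits (T = 0 to 5), within-person correlation 0.56, no school variation in change.
- d = |ln 0.7| × √3/π = 0.197, reached over five intervals, so the slope difference is 0.197/5 = 0.0393.
- 6 × Var(T) = 17.5, so SE = √[2(1 − 0.56)/(420 × 17.5)] = 0.0109 and z = 3.59.
- Power = Φ(3.59 − 1.96) = 94.9%.

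Multiplying the variance by 1 + 69 × ICC of change lowers this to 79% at ICC 0.01 and 64% at 0.02. This shows sensitivity to the missing term. It does not show what the authors assumed.

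**Type I error without a school-level time effect.** Students per school: m = 420/6 = 70 (from the article). ICC of change ρ: assumed. The true variance of an arm's mean change is 1 + (m − 1)ρ times the variance the model uses, so

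type I error = 2 × [1 − Φ(1.96/√(1 + (m − 1)ρ))].

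| ρ (assumed) | 1 + 69ρ | True SE / model SE | Type I error |
|---|---|---|---|
| 0 | 1.00 | 1.00 | 5.0% |
| 0.005 | 1.345 | 1.16 | 9.1% |
| 0.01 | 1.69 | 1.30 | 13.2% |
| 0.02 | 2.38 | 1.54 | 20.4% |

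Across ρ = 0.005, 0.01 and 0.02, m = 60 (3,360/42 = 80 recruited, less 25% attrition) gives 8.5%, 12.0% and 18.4%. With m = 80 the figures are 9.7%, 14.3% and 22.2%.

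**Simulated change scores, no intervention effect.** Setting: 36 schools × 70 students, binary ever-use of about 11% at baseline and 20% at 12 months (assumed). For a school SD of log-odds change of 0, 0.2, 0.4 and 0.6, a test without school-level change rejected in 5.7%, 7.5%, 12.9% and 21.4% of trials. A school-level test stayed at 4.8% to 5.1%.

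**Fitted logistic mixed models, no intervention effect.** This is the check closest to the written model. Setting: lme4 glmer with its fast approximation, 36 × 70 students, four visits to 12 months, 300 runs per row. Assumed SDs: school intercept 0.4, participant intercept 2, participant slope 0.5.

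| School SD of log-odds change (assumed) | No school slope | With school slope |
|---|---|---|
| 0 | 2.7% | 2.0% |
| 0.4 | 9.0% | 6.7% |
| 0.6 | 17.7% | 6.0% |

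The Monte Carlo standard error at 9.0% is √(0.09 × 0.91/300) = 1.7 points, so the contrast at SD 0.4 is modest. A smaller run of 90 gave lower rates: 2.2% against 1.1% at SD 0.3, and 7.8% against 2.2% at SD 0.6. Pooling both runs at SD 0.6 gives (53 + 7)/390 = 15.4% without the school slope and (18 + 2)/390 = 5.1% with it. The direction is the same in both runs; the size is less certain than the 17.7% suggests.

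**The case against.** The strongest reply is that the sentence is merely garbled. Nested intercepts for participant and school, followed by time as a random slope, could be shorthand for the lme4 term (time | school/participant). That puts a time slope at both levels and would largely cure the problem. This stands as a caution: the text does not prove what will be fitted. It does not rescue the text, which names no slope for school and can be read as either a sound or an anti-conservative primary model.

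It is also fair that the inflation depends on a variance the article does not report. With no school variation in change, the fitted models rejected no more than 5% of the time. Nor does the plan ignore schools altogether, so a simulation of a student-level test with no school term would not measure this model.

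A reader might further infer that the model is at fault for not naming the randomisation factors, given allocation "with stratification by state and school gender mix". The document does not support that. Intervention effects neither lists nor excludes fixed covariates, and an article may leave them to the analysis plan. Omitting them also works the other way: in simulation, type I error of a school-level test was 5.0%, 3.4% and 1.3% as stratum effects grew (SD 0, 0.5 and 1 times the school SD). That is conservative.

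**Conclusion.** The point holds in conditional form. The random-effects sentence is not a valid specification. Taken as written, it leaves school-level variation in change out of the standard error of the primary contrast, in a trial that randomises schools. The test is then anti-conservative whenever schools differ in change.

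The size rests on assumptions: roughly 9% to 20% for a nominal 5% test at an ICC of change of 0.005 to 0.02 with about 70 students per school, and nil at zero. The fitted-model checks agree in direction and are clear only at the larger assumed SD. A reader might infer that the primary test will certainly over-reject, or by a known amount. The article supports neither, because it gives no school-level variance of change and the authors may have intended a school slope.

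**What to change.** Replace the sentence with an explicit specification: a random intercept and a random time effect for school (a school-by-time random effect if time is categorical), and, for participant nested in school, a random intercept and, where estimable, a random time slope. With linear time, one lme4 form is (1 + time | school) + (1 + time | school:participant).

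A school-level analysis, or a small-sample correction for 36 to 42 schools, is a reasonable optional sensitivity check on the primary test.

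The cost is one sentence and the model code, with no change to design or data collection. The downside is that confidence intervals may be wider than under the model as printed.

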#### Cost-effectiveness

The base case analysis will be undertaken using a partial societal perspective, alongside an additional analysis from a health sector perspective. Area-under-the-curve methods will be applied to CHUD9D data to estimate the QALYs associated with the *OurFutures Vaping Program* and active control condition. The costs that accrue across each trial arm will be calculated as the sum of: all relevant intervention delivery costs; and the cost of utilising additional healthcare and other related services. The cost of delivering the *OurFutures Vaping Program* and health education as usual will be estimated based on a detailed accounting of resources required to deliver each respective program. This will consider all costs associated with intervention delivery and usual education, including staff and teacher time alongside program materials. Data from the RUQ will be used to estimate the cost of utilising additional healthcare and other related services. The cost-effectiveness of the *OurFutures Vaping Program* – when compared to health education as usual – will be evaluated using the incremental cost-effectiveness ratio (ICER) as the main measure of cost-effectiveness. That is, the difference in mean costs divided by the difference in mean QALYs between the intervention and control arms.

A cost-consequences analysis will also be done to produce a dashboard of all relevant costs and outcomes resulting in each trial arm. Additional cost-effectiveness ratios can then be estimated by adopting primary and secondary outcomes as the denominator (e.g., the cost per student not engaging in vaping behaviours and the cost per unit gained on the PHQ-8). Standardised economic evaluation techniques, such as Fieller’s theorem and non-parametric bootstrapping, will be used to estimate confidence intervals around each cost-effectiveness ratio. Economic modelling can also be undertaken, if applicable, to estimate the long-term costs and outcomes that may accrue beyond the timeframe of the cluster RCT and to estimate the cost-effectiveness and/or budget impact of scaling up the intervention across Australian schools.

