**ASSESSMENT**								
Primary Outcomes			X	X	X	X	X	X
Secondary Outcomes (except RUQ & SDQ)			X	X	X	X	X	X
Secondary Outcomes (RUQ & SDQ)			X	X		X	X	X
Process outcomes				X				

*Note: RUQ = Resource Use Questionnaire; SDQ = Strengths & Difficulties Questionnaire.*

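### The article defines cost per QALY from differences in arm means and names no adjustment for baseline CHU9D or baseline resource use, although both are collected

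*Protocol article*

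**What the plan says.** In the protocol article, the Cost-effectiveness section builds QALYs from the repeated utility scores: "Area-under-the-curve methods will be applied to CHUD9D data to estimate the QALYs" in each arm. It defines the main economic result, the ICER, as "the difference in mean costs divided by the difference in mean QALYs between the intervention and control arms". For uncertainty it says that standard techniques, "such as Fieller’s theorem and non-parametric bootstrapping, will be used to estimate confidence intervals around each cost-effectiveness ratio". It names no regression model or covariate for either the QALY or the cost difference.

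The Intervention effects section does deal with baseline. It describes the time-by-group effect for the primary outcome as the change in the intervention group "compared to control, adjusting for baseline differences". That wording is tied to the primary outcome and is not extended to the QALY area or to costs.

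The baseline data exist. Quality of life (CHU9D) is a secondary outcome, so it falls in the Table 1 row that begins "Secondary Outcomes (except RUQ & SDQ", which is marked at baseline and at all five later waves. The resource use questionnaire has its own row, which is also marked at baseline.

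On the number of clusters, the Randomisation section says: "Twenty-one schools will be randomly allocated to the *OurFutures Vaping Program* intervention group and 21 schools to an active control group". Stratification is by state and school gender mix only.

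**The concern.** An area under a utility curve carries the baseline level in two ways. The baseline score enters the first trapezoid directly, and every later score is correlated with it. If one arm's schools start with higher utility by chance, their students will tend to accumulate more QALYs with no programme effect. A crude difference in mean areas keeps that component; a regression on baseline utility removes most of it. The same reasoning applies to costs and baseline resource use.

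With 21 schools per arm, and no stratification on utility or socioeconomic status, some baseline difference is to be expected. The QALY difference is the denominator of the ICER. If it is small, a modest shift changes the ratio a great deal. CHU9D is also a secondary effectiveness outcome, so the same data could give a baseline-adjusted quality-of-life effect in one section and an unadjusted QALY difference in another.

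**Working it through.** **1. The plan's own figures.** The article gives no CHU9D SD, ICC, correlation, expected QALY gain or ICER, so there is no economic figure to reproduce. The recruitment target, which fixes the number of schools, can be checked:
- Students per state: 840 / (1 - 0.25) = 1,120, as stated.
- Schools per state: 12 / (1 - 0.15) = 14.1, stated as 14.
- Three states: 42 schools and 3,360 students, or 3,360 / 42 = 80 per school and 21 schools per arm.

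**2. Weight of each wave in the area.** With the Table 1 times (0, 5 weeks, 6, 12, 24 and 36 months), the trapezoid weights in years are 0.048, 0.250, 0.452, 0.750, 1.000 and 0.500, which sum to 3.0. The direct baseline weight is 0.5 x 5/52 = 0.048. Almost all the carry-over therefore comes through correlation of later waves with baseline, not through the baseline point itself.

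**3. Chance baseline difference.** SE = SD x sqrt[ (2 / (21 x 80)) x (1 + 79 x ICC) ].

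**4. Shift in the 36-month QALY difference for a one-SE imbalance.** Shift = SE x [0.048 + r x (3 - 0.048)], where r is the correlation of baseline with later waves.

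All values of SD, ICC and r below are assumptions.

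| SD | ICC | r | SE of baseline difference | Shift, 36 months | Shift, 12 months |
|---|---|---|---|---|---|
| 0.10 | 0 | 0.3 | 0.0035 | 0.003 | 0.001 |
| 0.20 | 0.03 | 0.5 | 0.0127 | 0.019 | 0.007 |
| 0.25 | 0.05 | 0.7 | 0.0192 | 0.041 | 0.014 |

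Middle row in full: 0.20 x sqrt(2/1,680 x 3.37) = 0.0127; then 0.0127 x (0.048 + 0.5 x 2.952) = 0.0127 x 1.524 = 0.019.

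Allowing for the planned losses (36 schools of 70 students) gives results inside the same range. SD 0.12, ICC 0.01, r 0.4 gives SE 0.0062 and shift 0.0076. SD 0.20, ICC 0.05, r 0.6 gives SE 0.0168 and shift 0.0306.

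**5. Null simulation.** There were 42 schools of 80 students, complete data, no true effect, SD 0.20 and student-level correlation 0.5, with 600 runs per scenario. Adjustment was on the student's own baseline score. The last column averages the runs in which the baseline difference favoured the intervention arm by more than 1 SD of its distribution.

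| ICC | School-level correlation | Mean, crude | SD of estimate, crude / adjusted | Mean given imbalance above 1 SD, crude / adjusted |
|---|---|---|---|---|
| 0.03 | 0.5 | 0.002 | 0.031 / 0.023 | 0.030 / -0.001 |
| 0.03 | 0.8 | 0.001 | 0.034 / 0.021 | 0.042 / 0.011 |
| 0.01 | 0.5 | -0.000 | 0.021 / 0.017 | 0.019 / -0.002 |

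In the first scenario the variance falls by 1 - (0.0227 / 0.0305)^2 = 45%. The crude mean is close to zero throughout, so there is no bias over randomisations. The shift appears only once the imbalance is taken as given. With school-level correlation 0.8, student-level adjustment cuts it from 0.042 to 0.011 but does not remove it.

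**The case against.** The strongest objection is that the article never calls the difference raw, crude or unadjusted. The ICER sentence is the ordinary definition of the ratio, and adjusted mean differences satisfy it equally well. The section reads as a summary, and the covariates of an economic analysis are often left to a fuller plan that is not shown. This stands in part. A reader might infer that the sponsor has chosen an unadjusted analysis, and the text does not support that. What remains is that the published estimator, followed as written, gives a crude difference, and a better one is available from data already scheduled.

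Second, CHU9D and resource use are secondary outcomes, and the mixed models are said to cover secondary outcomes. But the effect described there is a time-by-group interaction, not a difference in areas, and the remark on baseline adjustment concerns the primary outcome.

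Third, randomisation keeps the crude difference unbiased, and chance imbalance is sampling error that the planned intervals are meant to express. This is correct. The case for adjustment is precision, and protection given the imbalance actually seen. A reader might go further, note that Table 1 places student consent after allocation, and infer systematic imbalance. The article gives no evidence that student entry differs by arm, so the point does not rest on that.

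Fourth, every magnitude depends on assumed inputs, and the range spans more than tenfold. This also stands.

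**Conclusion.** The point holds as an improvement to the stated estimator. The Cost-effectiveness section names no adjustment for baseline CHU9D or baseline resource use, although both are collected and the primary effectiveness effect is described as baseline-adjusted. Read literally, the resulting QALY difference is unbiased on average but less precise than it need be. A one-standard-error chance imbalance would shift it by about 0.003 to 0.041 QALY over 36 months (0.001 to 0.014 over 12 months), under SD 0.10-0.25, ICC 0-0.05 and correlation 0.3-0.7.

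Two stronger conclusions are not supported. One is that the planned analysis is known to be unadjusted or wrong: the text is silent on this. The other is that baseline imbalance will determine the sign of the ICER: the article gives no expected QALY effect to set against these shifts, so one can say only that they could matter if the denominator is small.

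**What to change.** In the Cost-effectiveness section, or in the economic analysis plan if there is one, state three things:
- Incremental QALYs are estimated by regressing each student's area under the curve on arm and baseline CHU9D utility, and incremental costs by regressing cost on arm and baseline resource-use cost. Both models allow for clustering by school.
- These adjusted differences are used in the ICER and in its Fieller or bootstrap intervals.
- The crude difference is reported as a sensitivity result.

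If a fuller plan already specifies this, one clause in the article's definition of the ICER is enough. The cost is a sentence or two: both baseline measures are already scheduled in both arms, so no new data are needed and the sample size is unaffected. Fixing this before outcome data are seen also removes a later choice between crude and adjusted versions of the main economic result.
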